#### Exclusion criteria

The study interventions necessitate the exclusion of major causes of secondary constipation. In detail:Significant organic colonic disease (red-flag symptoms, e.g. rectal bleeding previously investigated); inflammatory bowel diseases; megacolon or megarectum (if diagnosed beforehand (the study will provide a useful estimate of the prevalence of such cases in referral practice)); severe diverticulosis/stricture/birth defects deemed to contribute to symptoms (incidental diverticulosis if known is not an exclusion)Major colorectal resectional surgeryCurrent overt pelvic organ prolapse (bladder, uterus) or disease requiring obvious surgical intervention other than LVMRPrevious rectopexySacral nerve stimulation (SNS) *in situ*Rectal impaction (as defined by digital and abdominal examination: these form part of the NHS Map of Medicine basic standard) (http://mapofmedicine.com/care-pathway-content-update-publication/)Significant neurological disease deemed to be causative, e.g. Parkinson’s, spinal injury, multiple sclerosis, diabetic neuropathy (not uncomplicated diabetes alone)Significant connective tissue disease, e.g. scleroderma, systemic sclerosis and systemic lupus erythematosus (not hypermobility alone)Significant medical comorbidities and activity of daily living impairment (based on Barthel index ≤11 in apparently frail patients)Major active psychiatric diagnosis, e.g. schizophrenia, major depressive illness and maniaChronic regular opioid use (at least once daily use), where this is deemed to be the cause of constipation based on temporal association of symptoms with onset of therapyPregnancy or intention to become pregnant during study periodKnown severe intra-abdominal adhesions

### Study procedures

#### INVEST radio-physiological investigations

Participants will have undergone standard (clinically routine) investigations to determine eligibility for surgery. However, some patients may have missed specific tests that are required to meet the INVEST standard of the overall programme (or not had tests conducted in last 12 months). In such cases, individual missing investigations will be performed to meet the standard below, with the exception of whole-gut transit studies. In order to avoid unnecessary repeated radiation, whole-gut transit studies performed in the last 12 months (even if using a different marker protocol) may be carried forward if a clear diagnosis of either delayed or normal whole-gut transit time has been confirmed.

Routine NHS practice (10-day NHS rule) will apply in respect of women between menarche and menopause. Participants who may potentially be pregnant will have a serum or urine pregnancy test performed as per routine care.

INVEST includes:Anorectal manometry using high-resolution methods [83–85] to determine defined abnormalities of rectoanal pressure gradient during simulated evacuation [36, 86, 87].Balloon sensory testing using standardised methods [88, 89] (2 ml air per second to maximum 360 ml) to determine volume inflated to first constant sensation, defaecatory desire and maximum tolerated volumes. Rectal hyposensation and hypersensation defined in accord to gender-specific normative data on 91 healthy adults [90]. The rectoanal inhibitory reflex will also be elicited by 50 ml rapid inflation (if necessary in 50 ml aliquots up to 150 ml).Fixed volume (50 ml) water-filled rectal balloon expulsion test [36, 86, 91, 92] in the seated position on a commode. Abnormal expulsion is defined as abnormal if failure to expel within 1.0 minute of effort for men and 1.5 minutes for women [93].Whole-gut transit study using serial (different-shaped) radiopaque markers over 3 days with single plain radiograph at 120 hours [77, 94].Fluoroscopic evacuation proctography using rectal installation of barium porridge to defaecatory desire threshold (or maximum 300 ml) and evacuation on a radiolucent commode [54, 83–85, 95] with pre-opacification of the small bowel (for enterocele). Radiation dose, proportion of contrast evacuated and time taken will be recorded, as well as “functional” (i.e. pelvic-floor dyssynergia) and “structural” features deemed obstructive to defaecation (e.g. rectocele, enterocele and intussusception) [36, 90].

Participants will be given the results of investigations by the physiologist or radiologist.

#### Laboratory assessments

Serum or urine pregnancy testing will be performed by local NHS biochemistry laboratories as per standard NHS policy prior to radiological and surgical procedures.

#### Pelvic-floor MDT confirmation

As part of the whole CapaCiTY programme, a national MDT has been convened to develop a standard set of criteria for surgical eligibility to be used by local MDTs. These criteria have been coalesced into a trial case report form (CRF) that will be used to validate eligibility for each patient before randomisation.

#### Randomisation procedures

Randomisation will be delivered following recruitment (after full eligibility and all baseline assessments). Randomisation will be stratified by sex and female participants further stratified by centre. The Pragmatic Clinical Trials Unit (PCTU) has developed a validated online randomisation system, which will be accessed by suitably trained and delegated researchers at recruiting sites and will follow the PCTU approved standard operating procedure (SOP) for the study.

#### Blinding

Patients and clinicians are necessarily aware of allocation to different waiting times. For quantitative analysis, an analysis plan will be developed and signed off by investigators and statisticians who are blind to allocation status and index intervention. No quantitative analysis will be undertaken until the analysis plan is signed off.

### Study interventions

#### Laparoscopic ventral mesh rectopexy (LVMR) (see Additional file 5)

Participants will attend for surgery at their allocated time with admissions procedures as per routine clinical care with normal preparation, e.g. bowel cleansing. Perioperative care will proceed with normal adjuncts (informed NHS consent, World Health Organization (WHO) surgical checklist, appropriate broad spectrum antibiotic prophylaxis, venous thromboembolism (VTE) prevention, patient warming and urinary catheter insertion). Surgery can be performed as a day-case procedure within an enhanced recovery programme [96], although most patients will have an overnight stay. Consent will include discussion of the risks of conversion to open surgery and specific complications listed below. A phosphate enema or similar (optional) may be used to clear the rectum.

The exact surgical technique will be surgeon-specific (based on individual preference) but in accord with expert guidance [73] and training. All participating surgeons will require sign-off by a delegated surgical team provided by the Pelvic Floor Section of the Association of Coloproctology. Where required, preceptorship will be provided to meet sign-off requirements (at the time of writing, all participating surgeons are experts in this technique).

In brief, after positioning the patient (modified lithotomy position on a non-slip mat) and port-site insertion (using standard equipment and technique), the rectosigmoid junction is retracted to the left and a peritoneal incision is made over the right side of the sacral promontory and extended in an inverted J-form along the rectum and over the deepest part of the pouch of Douglas. Special care is taken not to damage the right hypogastric nerve. Denonvillier’s fascia is incised and (in women) the rectovaginal septum is broadly opened. Limited rectal mobilization and lateral dissection is performed as required to expose the distal rectum and pelvic floor. A strip of trimmed mesh (biologic or synthetic) is inserted. Using non-absorbable or slowly absorbable sutures (polydioxanone (PDS) is recommended), the mesh is sutured to the ventral aspect of the distal rectum and further fixed to the lateral seromuscular borders of the rectum proximal and distal to the incised pouch of Douglas +/- pelvic floor. The mesh is fixed upon the sacral promontory using either sutures or an endofascia stapler. Limited traction is exerted on the rectum as required to obliterate the intussusception +/- rectocele. If deemed necessary, the posterior vaginal fornix may be elevated and sutured to the anterior aspect of the mesh; this allows closure of the rectovaginal septum and correction of a mid-compartment prolapse, if present. The lateral borders of the incised peritoneum are then closed over the mesh. This elevates the new pouch of Douglas over the colpopexy and completely covers the mesh with peritoneum. No drain is usually required. Ports should be closed directly (endoclose for lateral ports) owing to the high risk of early and late port site hernias in this group of patients with potential connective tissue laxity.

Post-operative management will be as per routine clinical care. This is usually an overnight hospital stay followed by urinary catheter removal, mobilisation and discharge. Post-operative laxatives use is standardised to a weaning course of Movicol/Laxido three times daily (TDS) immediately post-operative for 1 day, then reduced according to ease of bowel movements. Medication will be post-operatively recorded on a drug chart by the anaesthetists. This prevents post-operative constipation from immobility, narcotics and general anaesthesia, which if left untreated may cause painful straining on the mesh and thus protracts in the sacral promontory periosteum, potentially leading to readmission. The surgeon should aim to discharge patients 1 day post-operative. Length of stay will, however, be determined by clinical evaluation and may be longer if required. Quality control of LVMR procedures will be conducted according to expert panel review, as per the relative SOP.

#### LVMR 30-day follow up

Clinical recurrence of rectal prolapse will be determined based on physical examination. Morbidity and mortality data will be collected, in addition to treatment of any complications arising from LVMR surgery. The 30-day readmission rates will also be recorded. A CRF will be used to capture intra-operative and post-operative data (see surgery-specific outcomes).

#### Concomitant medications

It is inevitable that participants will seek recourse to laxatives and other dietary supplements during the course of the programme. Experience shows that complete prohibition can lead to unreported laxative use, which might confound findings. Although we will strongly discourage *ad libitum* medication usage and specify a defined breakthrough regimen, we will record co-treatment with sufficient fidelity and integrity to enable use as covariates in analyses using a specific diary for this purpose. A concomitant medications list including a shortlist of contributory or confounding medications will be used for filtering on data entry.

### Schedule of assessment (see Fig. 1)

**Fig. 1 Fig1:**
[figure not shown]
Standard Protocol Items: Recommendations for Interventional Trials (SPIRIT) diagram. *MDT* Multidisciplinary Decision Team, *IBSQ* Irritable Bowel Syndrome Questionnaire, *LVMR* Laparoscopic Ventral Mesh Rectopexy, *PAC-QOL* Patient Assessment of Constipation Quality of Life questionnaire, *PAC-SYM* Patient Assessment of Constipation Symptoms Questionnaire, *EQ-5D* EuroQol Health Outcome measure, *EQVAS* EuroQol visual analogue scale, *PHQ-9* Patient Health Questionnaire -9, *GAD7* Generalized Anxiety Disorder Questionnaire, *CC* chronic constipation, *BIPQ* Brief Illness Perception Questionnaire, *AE* adverse events, *ConMeds* concomitant medications, *V* visit, * POPQ* Pelvic Organ Prolapse Quantification System, *Rome IIIQ * constipation questionnaire based on the Rome III criteria, *CC-BRQ* Behavioural Response to illness Questionnaire

#### Visit 0 - Pre-screening: eligibility assessment

A suitably trained and delegated local researcher will screen for basic eligibility within outpatient clinics or by phone (or later face-to-face interview based on patient choice) on the basis of a simplified inclusion/exclusion criteria proforma, and listed for LVMR (in some cases/NHS settings based on preliminary MDT review). Participants will be recorded on a screening log and each will be allocated a sequential study number. Eligible participants will be provided with adequate explanation of the aims, methods, anticipated benefits and risks of the study and will take away or be posted an invitation letter and patient information sheet (PIS). Patients will be given at least 24 hours to consider participation.

The study screening number will be allocated as follows:Study code 03Site code – 3-letter code for each siteParticipant code – 4-digit code given consecutively and attributed at each site

For example, the first participant screened at Bart’s Health Trust would be assigned the code 03-BLT-0001. If they were then recruited to the study, they would retain this number.

#### Visit 1 - consent, screening, and baseline assessments

Visit 1 will be conducted face-to-face in the clinic or private research environment. Following a detailed discussion about the trial and review of the PIS, patients who are basically eligible and who agree to participate will complete written informed consent, followed by screening and confirmation of eligibility for randomisation by obtaining structured medical and surgical history and review of findings on physical examination. Thereafter, additional baseline outcome assessments will be conducted. These include several key validated assessments that profile patients for important characteristics informing disease pathophysiology and important potential predictors of treatment response. All have been selected on the basis of trade-off between adequate detail and achievable brevity. These instruments will be coalesced into a single booklet (he design and presentation have been optimised by patient representatives).

##### Screening/confirmation of eligibility

Screening and confirmation of eligibility will be performed as follows:Structured medical and surgical history obtained by interview, including medication usageClinical examination findings (carried forward if performed previously within the last 3 months): standardised examination of the perineum/anus/rectum/vagina including POP-Q assessment of rectoceleReview of clinical radio-physiological investigations (some further tests may be required to meet INVEST standard)Final review by pelvic floor MDT (as NHS England draft recommendation) to confirm appropriateness for surgery

##### Standardised outcome framework

The standardized outcome framework will comprise:PAC-QOL, PAC-SYM, EQ-5D-5L and EQVAS, PHQ9, GAD7, CC-BRQ, BIPQ-CC, St Marks Incontinence score, PISQ-12 in women and MSHQ-EjD Short Form in men)Baseline 2-week patient bowel diary and health economics journal will be given

##### Other baseline-only assessments

Other baseline-only assessments comprise:Constipation (2006) and IBS (2006) modules of the Rome III questionnaireCleveland Clinic constipation questionnaire [97]Brief, chronic pain, autonomic and joint hypermobility assessments

Randomisation will be performed only once full eligibility has been confirmed and all baseline assessments taken (which may require INVEST). Urinary pregnancy testing will be made available to women of child-bearing potential at eligibility assessment and advice will be given to all women on the need to prevent pregnancy during the study intervention period.

#### Visit 2 - run-in for surgical interventions

Participants will be randomized (at visit 1) to three arms with different lengths of delay before surgery. In all arms there will be a period of 4 weeks post-eligibility to arrange the logistics of surgery (T–4w to T0) and ensure that patients have returned to their normal life routine after various assessments. Subsequently, LVMR will be performed at T0 in group I (visit 2); T12 (12 weeks) in group II (visit 3) and T24 (24 weeks) in group III (visit 4).

#### Visit 2–8 - follow-up outcome assessments

All patients will complete the standardised outcome framework (inclusive of PAC-QOL and PAC-SYM) questionnaires at T–4, T0 and 12, 24, 36, 48, 60 and 72 weeks post run-in (see Additional file 2). This ensures that 24-week and 48-week post-surgery follow-up data on the primary and secondary outcomes are collected in all patients, whilst maintaining blinding of group allocation. Thereafter, participants will leave the study and return to “routine clinical care” as determined within their local NHS institution. During the first 24 weeks post-surgery patients will be quarantined from further intervention, excepting emergency interventions (e.g. for complications).

#### Participant withdrawal (including data collection/retention for withdrawn participants)

Individual participants will be able to drop out at any time during either the treatment or follow up. Data will be retained for intent-to-treat analysis from all participants after the point of consent and recruitment as outlined in the PIS:Withdrawal from treatment criteria (no further interventions but follow up data collected){ participants will be withdrawn from the study interventions if they develop any of the following exclusion criteria:Becomes pregnant or intends to become pregnant (only in baseline and intervention phases);Subsequently diagnosed with proven cause of secondary constipation e.g. Parkinson’s disease or bowel obstruction;Develops significant inter-current illness precluding participation;Develops acute psychological problem causing safety concern;Elective withdrawal.Loss to follow up (no further interventions or follow up data collected): participants may be withdrawn from the trial if:They become lost to follow up (LTF) after at least three failed attempts by research staff to make contact via two different methods (e.g. phone and letter);Participant choses to withdraw and does not wish to participate in follow-up data collection;Participant dies or has significant incapacity making follow-up data collection impossible.

#### End-of-study definition

The end of study is defined as the last patient last visit (LPLV). The sponsor, Research Ethics Committee (REC) and local Research and Development (R&D) departments will be informed of the end of study and site closure and archiving procedures will be initiated.

#### Criteria for early termination

If the Data Monitoring and Ethics Committee (DMEC), PSC, REC or sponsor determine it is within the best interests of the participants or trial to terminate the study, written notification will be given to the CI. This may be due to, but not limited to; serious safety concerns, serious breaches, acts of fraud, critical findings or persistent non-compliance that negatively affects patient safety or data integrity. If the study is terminated, participants will be returned to the NHS normal follow up and routine care.

### Data management

The data collected for the trial will be a mixture of routinely collected data, verifiable against the medical records and patient-reported outcome measures (PROMs) or questionnaire data, collected directly in the CRF.

Each recruiting site will be required to keep accurate and verifiable source notes in the medical record relevant to each study participant’s inclusion and continued participation in the study. Data will be collected, transferred and stored in accordance with Good Clinical Practice (GCP) guidelines and data protection requirements. The PCTU SOPs and study data management plan will define the exact process of data collection, transfer and storage and control of study data.

All patient identifiable data, such as consent forms, screening and identification logs will be stored in the investigator site files in secure locked cabinets and/or offices, accessible only to delegated members of the study team. Secure methods of data transfer will be used to return CRFs to the coordinating site for centralized data entry, monitoring, quality control and compliance. A copy of the CRF will be held at the site in accordance with GCP.

A secure online “OpenClinica” trial database will be provided by the PCTU to enable remote data entry of CRFs at sites where this is feasible. This database will provide built-in data validation checks with quality control checks performed by checking a predefined percentage of CRF data against data entered into the database. In addition, on-site monitoring will enable source document verification of records.

The full data set will be collected face to face wherever possible to maximise completeness of data. However, to minimise bias, where possible, a blinded researcher will collect outcome data. Alternatively, the participant will enter outcome data directly into the e-CRF portal for patient-reported outcomes (REDCAP). An automated e-mail reminder will be sent to participants to remind them to complete the questionnaires and diaries every 12 weeks. Telephone or postal follow up will be permitted if necessary. At least three attempts via two different methods (e.g. phone and letter) will be made by research staff to make contact and collect follow-up data, after which the participant may be considered LTF if appropriate (see criteria for withdrawal).

#### Confidentiality

Information related to participants will be kept confidential and managed in accordance with the Data Protection Act, NHS Caldecott Principles, The Research Governance Framework for Health and Social Care and the conditions of REC approval.

Identifiable information to be collected from the participants includes full name, date of birth (DOB), hospital number and contact details at screening. This information will be used to contact participants but will not leave the study site without prior consent. All CRFs will be pseudonymised. The participant’s GP will be informed of their participation in the study, but they may opt out at the time of consent.

The trial data will be made available to suitably qualified members of the research team, study monitors and auditors, the REC and regulatory authorities as far as required by law. The participants will not by identifiable with regards to any future publications relating to this study.

#### Record retention and archiving

When the research trial is complete, it is a requirement of the Research Governance Framework and Sponsor Policy that the records are kept for a further 20 years. For trials involving Barts Health Trust patients, undertaken by Trust staff, or sponsored by BH or Queen Mary, University of London (QMUL), the approved repository for long-term storage of local records is the Trust Modern Records Centre.

Each site will be required to archive local site files and patient identifiable information such as consent forms and screening logs for a period of 20 years. At the end of the 20 year retention period, the Records Management team will alert R&D that the records are due for disposal. The chief investigator (CI) and sponsor will be informed and the full agreement of everyone concerned will be obtained before any records are destroyed.

### Statistical considerations

#### Sample size

The sample size has been calculated using the primary clinical outcome, a change in mean PAC-QOL score [74]. This widely used, psychometrically robust measure of overall treatment response with concurrent validity for patient global ratings of success has been used in previous trials of behavioural therapies and surgical trials [52] (including trials of LVMR) in CC [75]. For a chronic condition such as CC, a difference of 1.0 point in the primary outcome (score range = 1–4) can be considered clinically important and also the notional minimum required to justify the cost and invasive nature of LVMR, or of a more complex and expensive treatment.

Previous trials have shown a 1-point decrease in PAC-QOL from pre-operative to 48 weeks (1 year) post-surgery [52]. Using a stepped-wedge design, we hypothesize that PAC-QOL score at any time point during follow up will be approximately 1.0 point lower than in participants pre-operatively.

Sample size was calculated by simulation using the simsam package in Stata [98]. We assumed PAC-QOL follows a normal distribution over all time points with a standard deviation of 1.5 and with correlation between repeated assessments equal to 0.5.

Simulation shows that detection of a 1.0-point difference in 6-month PAC-QOL, with 95% power (purposely chosen to reflect the magnitude and risk of the intervention) at the 5% significance level, requires 34 participants in each of the three arms. Allowing for a 10% loss to follow up, a sample size of 38 is needed per arm (i.e. a total sample size of 114 patients across the three arms). Should the correlation between repeated assessments be lower than 0.5, a sample size of 114 will still provide at least 90% power for the study. This was calculated using the same simulation procedure with correlations of 0.3 and 0.1.

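### The sample size section gives PAC-QOL a range of 1–4 but assumes a normal score with SD 1.5 and a 1.0-point fall; these cannot all hold, so the range or the SD is misstated

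*Protocol article*

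**What the plan says.** All the relevant statements are in the protocol article under Sample size.

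- The scale and the target difference: "a difference of 1.0 point in the primary outcome (score range = 1–4) can be considered clinically important".
- The distribution: "We assumed PAC-QOL follows a normal distribution over all time points".
- The SD and the correlation: "with a standard deviation of 1.5 and with correlation between repeated assessments equal to 0.5".
- The target: "detection of a 1.0-point difference in 6-month PAC-QOL, with 95% power", at the 5% level, for which 34 per arm are said to be needed. A 10% allowance for loss makes this 38 per arm, 114 in total.
- The sensitivity check, said to leave at least 90% power at 114: "This was calculated using the same simulation procedure with correlations of 0.3 and 0.1".

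The section gives no source for the SD and does not relate it to the range.

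**The concern.** A score confined to an interval has a largest possible SD, half the width of the interval. For 1–4 that is exactly the 1.5 assumed. A score that is normal at every visit, keeps that SD before and after surgery and drops by a full point cannot exist on the stated scale.

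The SD matters because the required number scales with its square. If 1.5 does not belong to this scale, the 95% power, the 34 per arm and the implied smallest detectable difference do not describe the trial. The protocol says the 95% was chosen on purpose, to reflect the magnitude and risk of the operation, so readers will rely on it.

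**Working it through.** **Inputs from the protocol.** Sample size: range 1–4, normal score, SD 1.5, correlation r = 0.5 (also 0.3 and 0.1), difference 1.0, power 95%, 5% level, 34 per arm, 10% loss. Design/methods: three equal arms with surgery at T0, T12 and T24. Methods of analysis: mixed linear model on T0, T12, T24, T36 and T48, with the 24-week post-surgery comparison primary.

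**Assumptions made for the check.** Two-sided test, equal correlation between all visits, T0 score taken as pre-surgery in every arm, and separate effects at 12, 24, 36 and 48 weeks after surgery.

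**1. Reproduce the stated figure.** Under this model with r = 0.5, generalised least squares gives the variance of the 24-week effect as 1.15 × SD² / n, with n per arm. Hence

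n = 1.15 × SD² × (1.960 + 1.645)² / 1.0² = 1.15 × 2.25 × 12.995 = 33.6, so 34 per arm.

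With 34 per arm, SE = √(1.15 × 2.25 / 34) = 0.276 and power = Φ(1/0.276 − 1.96) = 95.2%. Then 34 / 0.9 = 37.8, so 38 per arm. With 38 per arm, power is 94.5% at r = 0.3 and 94.6% at r = 0.1, in line with the claim of at least 90%. The arithmetic is therefore right for its inputs, and SD 1.5 is the input behind the stated numbers.

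**2. Is SD 1.5 compatible with 1–4?**

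- Overall ceiling: (4 − 1)/2 = 1.5, reached only at mean 2.5 with half the patients scoring 1 and half scoring 4.
- Ceiling at mean m: √((m − 1)(4 − m)). At m = 3 it is √(2 × 1) = 1.41, and at m = 2 it is √(1 × 2) = 1.41.
- Two means 1.0 apart cannot both be 2.5. Placing them at 3 and 2 is the most favourable choice; any other lowers the ceiling for at least one of them. So SD 1.5 both before and after a 1.0-point fall is impossible.
- A normal score with mean 2.5 and SD 1.5 has 2 × Φ(−1) = 31.7% of its values outside 1–4.

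**3. What changes if the range is right.** Hold r = 0.5, the 24-week contrast and 95% power. Then n = 33.6 × (SD/1.5)². With 34 per arm, SE = √(1.15 × SD² / 34), power for 1.0 point is Φ(1/SE − 1.96), and the difference detectable with 95% power is 3.605 × SE.

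| SD | Basis | n per arm for 95% power | Power with 34 per arm | Detectable difference with 34 per arm |
|---|---|---|---|---|
| 1.5 | as stated | 34 | 95.2% | 0.99 |
| 1.41 | ceiling at means 3 and 2 | 30 | 97.0% | 0.94 |
| 1.25 | assumption | 24 | 99.2% | 0.83 |
| 1.0 | assumption | 15 | above 99.9% | 0.66 |
| 0.87 | assumption (uniform on 1–4) | 12 | above 99.9% | 0.58 |

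**4. What changes if the SD is right and the range is the slip.** The range is not an input to the simulation, so 34 per arm and 95% power stand. For example, on a 0–4 scale (an assumption; the document does not give it) the ceiling would be 2.0 and SD 1.5 would be possible, although a normal score centred at 2 would still have 18% of its values off the scale.

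**The case against.** The range is a descriptive aside and the simulation never used it. If the aside is the slip, the sample size is untouched. This stands: the document does not settle which figure is wrong, so it would go too far to say that the SD is the error. Nor is SD 1.5 impossible by itself. It is attainable at the bound, and only its combination with normality and a 1.0-point shift is not.

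Normal approximations for bounded questionnaire scores are also routine, so the share of values off the scale is secondary. That is fair; the conflict rests on the SD ceiling.

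A reader might infer three stronger points that the documents do not support.

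- *Any SD that fits 1–4 leaves the trial sized for a much smaller difference.* At SD 1.41 about 30 per arm are still needed and the detectable difference is 0.94. The larger shifts depend on assumed SDs.
- *The SD is why a difference below 1.0 point could reach significance.* With exactly 95% power for 1.0 point, an observed difference of 1.96/3.605 = 0.54 is already significant at SD 1.5. Any superiority trial powered this way shares that property, so it gives no ground for asking that the confidence interval be judged against 1.0.
- *Too many patients will undergo surgery, so the target must fall.* No admissible SD is documented from which a smaller target could be set, and the correction asked for here leaves recruitment as it is.

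**Conclusion.** The point holds as an internal contradiction: a 1–4 range, a normal score with SD 1.5 at all time points and a 1.0-point fall cannot all be true. Either the range or the SD is misstated, and the SD is unsourced.

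If the range is right, the error is conservative. The requirement lies between about 30 per arm at the extreme SD of 1.41 and 12 at an assumed 0.87, against 34 stated. Power with 34 per arm is 97.0% or more, so the trial is not underpowered on this account. If the range is wrong and the SD right, the stated figures stand. The sizes rest on the model that reproduces the protocol's 34 per arm, on r = 0.5 and on the labelled SDs. The validity of the primary analysis does not depend on the planning SD.

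**What to change.** Under Sample size, correct whichever of the range and the SD is wrong, and give the source of the SD. Re-run the existing simulation with an SD admissible on the corrected scale. One source is the trial itself: recruitment is ongoing and PAC-QOL is collected at T–4 and T0, so a pooled baseline SD and a T–4/T0 correlation can be estimated without reference to arm. Those two assessments are only four weeks apart, so the lower correlations of 0.3 and 0.1 should stay as sensitivity values. Then restate the power and the difference detectable with 95% power at 114 patients (38 per arm, 34 after 10% loss).

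The cost is one re-run of an existing simulation and a change of wording. Recruitment and the primary analysis are unaffected.
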